### 2.2.7 Benefit/Risk Assessment

The 9vHPV vaccine has been shown to be beneficial and efficacious in preventing persistent anogenital HPV infection and disease associated with the 9 HPV types (6, 11, 16, 18, 31, 33, 45, 52, and 58). The frequency, severity, and magnitude of AEs identified in previous studies and post-marketing surveillance support a favorable benefit-risk analysis for the 9vHPV vaccine in the study population. In this study, the 9vHPV vaccine will be administered in the same 3-dose regime as currently used for the vaccination of girls through the Spanish National HPV Immunization Program^38.

Study subjects will benefit from participating in the study by receiving the 9vHPV vaccine, which is currently not included in the Spanish National Immunization Program for adult women. Although vaccination is unable to eliminate HPV infections already present, most HPV infections are cleared after 12-24 months, thus vaccination with 9vHPV will confer protection for future HPV persistent infections in women enrolled in the study.

Study subjects will also benefit from a gynecological examination by trained and experienced medical personnel, who may refer her for appropriate care and treatment.

## 3 HYPOTHESES, OBJECTIVES AND ENDPOINTS

| Objectives                                                                                                                                                                                                       | Endpoints                                                                                                                                                                                                                                                         |
|------------------------------------------------------------------------------------------------------------------------------------------------------------------------------------------------------------------|-------------------------------------------------------------------------------------------------------------------------------------------------------------------------------------------------------------------------------------------------------------------|
| 1) Primary Objective. To demonstrate that vaccination with a 3-dose regimen of 9vHPV will reduce viral infectivity in cervical, anal, urine, vulvar and oral samples from HPV 16/18/16+18-positive women. | 
 
In-vitro infectivity evaluation (by expression of E1+E4 HPV biomarker in HaCaT keratinocytes) of cervical, anal, urine, vulvar and oral samples collected before and after 9vHPV vaccination.
 
 |

|                                                                                                                                                                                                                                                                                                                                                                                                                                                                                                   |                                                                                                                                                                                                                                                                                                                                                                                                                                                                                                                                                                                                                                                                                                                                                                                                                                                                                                                                                                                                                                                                                                                                       |
|---------------------------------------------------------------------------------------------------------------------------------------------------------------------------------------------------------------------------------------------------------------------------------------------------------------------------------------------------------------------------------------------------------------------------------------------------------------------------------------------------|---------------------------------------------------------------------------------------------------------------------------------------------------------------------------------------------------------------------------------------------------------------------------------------------------------------------------------------------------------------------------------------------------------------------------------------------------------------------------------------------------------------------------------------------------------------------------------------------------------------------------------------------------------------------------------------------------------------------------------------------------------------------------------------------------------------------------------------------------------------------------------------------------------------------------------------------------------------------------------------------------------------------------------------------------------------------------------------------------------------------------------------|
| 
Hypothesis. 9vHPV promotes the production and exudation of anti-HPV antibodies, which neutralize new HPV16/18 virions and reduce the infective capacity of body fluids in HPV-positive women and the transmission of HPV infection.
                                                                                                                                                                                                                                                 | 
 
● Detection of HPV 6/11/16/18/31/33/45/52/58 L1 antibodies in cervical, anal, urine, vulvar and oral samples collected before and after 9vHPV vaccination, using             
 
– ELISA for types 16 and 18 in samples from RIFT-HPV 1 and 2 study cohorts,
 
– cLIA for all 9vHPV-covered types samples from RIFT-HPV 1 study cohort.
 
 
 
 
This endpoint will allow to associate the reduction in viral infectivity with the presence of neutralizing antibodies.
 
 
● HPV16/18 virion detection (using ELISA, electronic microscopy) and HPV DNA detection and genotyping (using Anyplex HPV28) in cervical, anal, urine, vulvar and oral samples collected before and after 9vHPV vaccination.
 
 
This endpoint will allow to identify samples of subjects with a non-productive viral infection or undergoing natural clearance, and distinguish them from samples of subjects with productive but reduced infection due to 9vHPV vaccination.
 |
| 
2) Secondary Objective. To summarize antibody responses to vaccination (GMT and seroconversion percentages) for each of the 9vHPV-covered HPV types (6, 11, 16, 18, 31, 33, 45, 52, and 58)
 
Hypothesis. A higher level of anti-HPV antibodies is expected after 9vHPV vaccination than after a natural serological response to an HPV infection. Anti-HPV antibodies titration will allow to identify subjects with natural serological responses before vaccination.
 | 
 
● HPV 6/11/16/18/31/33/45/52/58 L1 antibody titration in serum samples collected before and after 9vHPV vaccination, using             
 
– ELISA for types 16 and 18 in samples from RIFT-HPV 1 and 2 study cohorts,
 
– cLIA for all 9vHPV-covered types in samples from RIFT-HPV 1 study cohort.
 
 
 
                                                                                                                                                                                                                                                                                                                                                                                                                                                                                                                                                                                                                                                                                                                   |
| 
3) Tertiary/ Exploratory Objective. To demonstrate viral infectivity reduction in cervical, oral, urine, vulvar and anal samples from HPV 16/18/16+18-positive
                                                                                                                                                                                                                                                                                                                      | 
 
● Same endpoints as in primary objective.
 
                                                                                                                                                                                                                                                                                                                                                                                                                                                                                                                                                                                                                                                                                                                                                                                                                                                                                                                                                                                                                                           |

|                                                                                                                                                                                                                                                                                                                                                                     |  |
|---------------------------------------------------------------------------------------------------------------------------------------------------------------------------------------------------------------------------------------------------------------------------------------------------------------------------------------------------------------------|--|
| 
women before and after vaccination with 1-dose or 2-dose regimen of 9vHPV.
 
Hypothesis. Since serological response after administration of 2 vaccine doses is not inferior to 3 doses, infectivity reduction in cervical, anal, vulvar, urine and oral samples is expected to be detected after 2 doses, and at least partially after one dose.
 |  |
|---------------------------------------------------------------------------------------------------------------------------------------------------------------------------------------------------------------------------------------------------------------------------------------------------------------------------------------------------------------------|--|

## 4 STUDY DESIGN

### 4.1 OVERALL DESIGN

The main objective of the study is to demonstrate the reduction in infective capacity of body fluids (cervical, anal, urine, vulvar and oral samples) in adult women at least HPV 16 and/or 18 positive after vaccination with 9vHPV in a three-dose regimen.

The study's secondary/ tertiary objectives are the following:

- To determine HPV antibody levels before and after vaccination (GMT and seroconversion percentages) for each of the 9vHPV-covered HPV types (6, 11, 16, 18, 31, 33, 45, 52, and 58).
- To demonstrate viral infectivity reduction in cervical, oral, urine, vulvar and anal samples from women positive for at least HPV 16 and/or 18 HPV before and after vaccination with 1-dose or 2-dose regimen of 9vHPV.

A minimum of 39 and 30 subjects will enroll in two different study population cohorts, respectively:

#### RIFT-HPV 1 cohort:

- Non-vaccinated adult women aged 18 years or older, positive on cervix for HPV 16 and/or 18 with non-apparent cervical lesion or with cervical intraepithelial neoplasia (CIN) 1/2 lesion on cytology or biopsy, eligible for **conservative treatment**.

#### RIFT-HPV 2 cohort:

- Non-vaccinated adult women aged 18 years or older, positive for HPV 16 and/or HPV 18 anal test with non-apparent anal lesions or with anal lesions eligible for **conservative treatment**.
- Or non-vaccinated adult women aged 18 years or older, positive for HPV 16 and/or HPV 18 cervical test with vulvar premalignant lesion or condylomas, associated to HPV infection.

Candidates will be selected to participate according to the HPV DNA test result in a sample taken in their routine gynecological follow-up visit in:

- The Gynaecology Unit of the Bellvitge's University Hospital, which is designated as the study site, and where all study procedures are to be performed by the Sub-investigator and Study Nurse.
- those sites designated as satellite, which will contribute to the study only in subject's refer to study site to evaluate her enrolment:
  - The Oncologic Gynaecology Unit of the Mar Health Park (Study Investigator: [name]).
  - The Sexual and Reproductive Health Care Centre-ASSIR Delta del Llobregat (Study Investigators: [name] and [name]).
  - The Infections Unit of the Bellvitge's University Hospital (Study Investigators: [name], [name]).
  - the Cervical Cancer Screening Technical Office as part of Cervical Cancer Early Detection Programme of Cancer Epidemiology Research Programme of Catalan Institute of Oncology (Study Investigator: [name])
- The patients know the Study through our spreading of information material (mailing, posters, flyers,...) and they contact to Study team.

Information of study Investigators and sites is detailed in section [1.3](#).

Those women with a at least HPV 16 and/or 18-positive result and matching the baseline characteristics defined for RIFT-HPV 1 or 2 study cohorts will be invited to participate in the study by the Principal Investigator in the study site or the Investigators in the study's satellite sites. After explaining the objectives and procedures of the study to pre-selected candidates and answer their questions, Investigators of satellite sites will offer them to sign a Personal Data Usage Authorization Form (annex [11.3](#)) where they agree to be contacted by the study coordinator to make an appointment for the study's Visit 1 in the study site.

During Visit 1, eligibility criteria defined in section [5](#) will be reviewed with subjects after they read the Subject's Information Sheet and sign the Informed Consent Form (annex [11.2](#)). Those subjects complying with inclusion and exclusion criteria will be enrolled in the study and included in RIFT-HPV 1 or 2 study cohorts according to baseline characteristics.

All enrolled subjects will complete the specified procedures in 4 study visits: Visit 1/Day 1, Visit 2/Month 2, Visit 3/Month 6, and Visit 4/Month 7. Study procedures and time windows for each visit are summarized in the Schedule of Activities (section [1.2.2](#)).

9vHPV vaccine will be administered in Visits 1, 2 and 3 by a qualified health professional (Study nurse/Sub-Investigator).

There is no control group in this study: all subjects signing the Informed Consent Form will receive 9vHPV vaccination in a three-dose regimen as per protocol (section [8.1.9](#)) and therapeutic indication.

All enrolled subjects will follow the study procedures summarized below as per protocol (section [1.2.2](#)):

- Pregnancy test on a urine sample in Visits 1, 2, 3 and 4 before receiving any vaccine or collecting any sample.
- Completion of a questionnaire in Visits 1 and 4.
- Cervical, vulvar and anal sample collection by the study Investigator, and oral, urine and blood sample collection by the study nurse. All samples will be collected in Visits 1, 2 and 3 before receiving 9vHPV vaccination, and in Visit 4.
- Intramuscular administration of 9vHPV in a three-dose regimen in Visits 1, 2 and 3.

The following study laboratory procedures will be applied to samples obtained from study subjects:

- Assessment of HPV infectivity. Analysis of E1+E4 HPV biomarker expression in HaCaT keratinocytes in-vitro after exposure to cervical, anal, urine, vulvar or oral samples from all study subjects.
- Assessment of HPV positivity. Detection of HPV16 and 18 in cervical, anal, urine, vulvar and oral samples from all study subjects, using ELISA/electron microscopy to detect HPV virions, and HPV test/genotyping (Anyplex HPV28) to detect HPV DNA.
- Assessment of HPV immunogenicity. Detection and titration of anti-HPV L1 antibodies in serum, cervical, anal, urine, vulvar and oral samples from all study subjects, using ELISA for types 16 and 18 in samples from RIFT-HPV 1 and 2 study cohorts, or cLIA for all 9vHPV-covered types in samples from RIFT-HPV 1 study cohort.

Study subjects will be followed thorough the whole duration of the study for possible injection-site AEs, systemic AEs, SAEs and deaths regardless of causality. All AEs and SAEs will be recorded by the study Investigator at each study visit (section 8.4).

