### 1.2.2 Schedule of Activities (SoA)

|                                             | Day 1   | Month 2
(±3 weeks) | Month 6
(±4 weeks) | Month 7
(-3 weeks/
+7 weeks
from Visit 3) |
|---------------------------------------------|---------|-----------------------|-----------------------|----------------------------------------------------|
|                                             | Visit 1 | Visit 2               | Visit 3               | Visit 4                                            |
| Sign Informed Consent                       | ✓       |                       |                       |                                                    |
| Review eligibility criteria                 | ✓       |                       |                       |                                                    |
| Urine sample and pregnancy test performance | ✓       | ✓                     | ✓                     | ✓                                                  |
| Temperature (fever ≥ 37.8°C)                | ✓       | ✓                     | ✓                     | ✓                                                  |
| Questionnaire                               | ✓       | ✓                     | ✓                     | ✓                                                  |
| Height and weight measurement               | ✓       |                       |                       |                                                    |

|                                                                                                                                                |   |   |   |   |
|------------------------------------------------------------------------------------------------------------------------------------------------|---|---|---|---|
| Medical history, past and current medication and vaccination                                                                                   | ✓ | ✓ | ✓ | ✓ |
| Gynecological examination in routine visit                                                                                                     | ✓ | ✓ | ✓ | ✓ |
| Cervical sample collection                                                                                                                     | ✓ | ✓ | ✓ | ✓ |
| Vulvar sample collection                                                                                                                       | ✓ | ✓ | ✓ | ✓ |

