| Anal sample collection                                                                                                                         | ✓ | ✓ | ✓ | ✓ |
| First-void urine collection                                                                                                                    | ✓ | ✓ | ✓ | ✓ |
| Oral sample collection                                                                                                                         | ✓ | ✓ | ✓ | ✓ |
| Blood sample collection                                                                                                                        | ✓ | ✓ | ✓ | ✓ |
| Vaccination + 30 min monitoring for post-vaccination immediate adverse events                                                                  | ✓ | ✓ | ✓ |   |
| AE/SAE assessment                                                                                                                              |   | ✓ | ✓ | ✓ |
| Laboratory analytical procedures                                                                                                               |   |   |   |   |
| HPV infective capacity in-vitro evaluation (E1^E4-HaCaT model)                                                                                 | ✓ | ✓ | ✓ | ✓ |
| Anti-HPV 6/11/31/33/45/52/58 L1 ab detection/titration by cLIA in cervical, anal, oral, urine, vulvar and blood samples from RIFT/HPV 1 cohort | ✓ | ✓ | ✓ | ✓ |
| Anti-HPV 16/18 L1 ab detection/titration by ELISA in cervical, anal, oral, urine, vulvar and blood samples from RIFT/HPV 1 and 2 cohorts       | ✓ | ✓ | ✓ | ✓ |
| HPV test and genotyping (Anyplex HPV28) in cervical, anal, urine, vulvar and oral samples                                                      | ✓ | ✓ | ✓ | ✓ |

|                                                                                                            |   |   |   |   |
|------------------------------------------------------------------------------------------------------------|---|---|---|---|
| HPV16/18 virion detection (ELISA, electronic microscopy) in cervical, anal, urine, vulvar and oral samples | ✓ | ✓ | ✓ | ✓ |
|------------------------------------------------------------------------------------------------------------|---|---|---|---|

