#### 2.2.4 Antibody and viral particle detection in body fluids and models to assess viral infectivity

Previous studies have shown that anti-L1 antibodies are present in cervicovaginal and oral fluids in vaccinated women, in asymptomatic men or women with a positive serology for HPV16, and in oral mucosal transudates from HIV/HPV-positive individuals.

Vaccine-induced HPV antibodies originating from cervicovaginal secretions have also recently detected in first-void (FV) urine. Discharged mucus and debris from exfoliated cells from the female genital organs accumulate around the urethra opening, between the small labia, and are washed away mainly with the urine initial flow (first-void urine).

Moreover, new viral particles are present in body fluids obtained from individuals showing a productive HPV infection and HPV DNA has been detected in first-void urine. Although the direct interaction between antibodies and viral particles has not been demonstrated so far in the same group of HPV-positive individuals, the simultaneous detection of viral particles and anti-L1 antibodies in cervical, anal, vulvar and oral fluids suggest that anti-L1 antibodies, despite being unable to suppress the production and release of new viral particles, could decorate the viral capsid and limit their infectivity. As the vaccine VLPs induce a higher antibody response compared to natural serological responses, it could be expected that the interaction between anti-L1 antibodies and new produced viral particles, and therefore, viral neutralization, will be more effective in vaccinated women. In line with this, an evaluation of HPV transmission among heterosexual couples in the HITCH prospective cohort yielded a reduced transmission associated to vaccinated women, and a currently ongoing clinical trial is evaluating the effect of vaccination on the reduction of HPV DNA positivity incidence in sexually active couples ([NCT01824537](#)). However, new assays to functionally assess the reduction of infective capacity are indispensable to distinguish the effect of the vaccine on the prevention of new infections, from the effect on the infective capacity and transmission of HPV infections already present before vaccination.

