#### 8.2.1.3 First-Void Urine Sample Collection

One first-void urine sample will be collected from study subjects on each of the four visits for assessment of infectivity in HaCaT assay, HPV DNA testing and genotyping and detection of anti-HPV antibodies. On Visits 1 to 3, first-void urine sample will be collected before study vaccine's dose administration.

First-void urine sample will be collected using a Coli-Pee collector after at least 2h without voiding.

Once collected, urine samples will be stored at 4-10 °C for short-term preservation until start of lab procedures (within 48h of collection), or at -80°C for long-term storage.

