### 8.3.2 Pregnancy test

A urine sample will be collected from candidates in Visits 1 to 4, to perform a pregnancy test by the study personnel. A positive result will exclude the candidate from participation in the study.

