#### **9.1.1.2 Data analysis**

Differences in the infectivity rate before (Day 1/ Visit 1) and after vaccination (Month 7/ Visit 4) will be compared in cervical, anal, vulvar, urine and oral samples using non-parametric Wilcoxon signed rank test.

For cervical samples, joint and stratified analysis for HPV-RIFT1 and HPV-RIFT2 cohorts will be done.

Oral, vulvar, urine and anal samples included in the HPV-RIFT1 and HPV-RIFT2 cohorts will be analyzed together to obtain the minimal sample size established for this analysis. If sample size would allow stratified analysis for HPV-RIFT1 and HPV-RIFT2 cohorts, it will be performed and submitted.

Sensitivity analysis including only cases showing negative seroconversion before vaccination will be performed.

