## 11 ANNEX

### 11.1 STUDY QUESTIONNAIRE

| RIFT-HPV QUESTIONNAIRE                                             |                               |                                 |                                |                                |
|---------------------------------------------------------------------------|-------------------------------|---------------------------------|--------------------------------|--------------------------------|
| Visit date: ____/____/____                                         |                               |                                 |                                |                                |
| Visit 1/ Day 1                                                            | Visit 2/ Month 2              | Visit 3/ Month 6                | Visit 4/ Month 7               |                                |
| PERSONAL INFORMATION                                               |                               |                                 |                                |                                |
| Name: _____                                                               |                               |                                 |                                |                                |
| Birth date: ____/____/____                                                |                               |                                 |                                |                                |
| Gender                                            | Male  | Female  | Other  |                                |
| Date of last menstruation period: ____/____/____                          |                               |                                 |                                |                                |
| Time since last urination (before taking the FV sample): _____            |                               |                                 |                                |                                |
| Time since last thorough douching: _____
(before taking the FV sample) |                               |                                 |                                |                                |

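### As written, the pregnancy-test urine comes before the first-void study urine at every visit, with no wait or split void stated, so the collection order works against the protocol's own 2-hour rule

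*Protocol*

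**What the plan says.** Four places in the protocol govern urine collection.

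- Section 4.1 (Overall Design), in the list of procedures for all enrolled subjects: "Pregnancy test on a urine sample in Visits 1, 2, 3 and 4 before receiving any vaccine or collecting any sample". The same list names urine among the study samples.
- Section 1.2.2 (Schedule of Activities) has one row for "Urine sample and pregnancy test performance" and another for "First-void urine collection". Both are ticked at all four visits.
- Section 8.3.2: "A urine sample will be collected from candidates in Visits 1 to 4, to perform a pregnancy test by the study personnel".
- Section 8.2.1.3: "First-void urine sample will be collected using a Coli-Pee collector after at least 2h without voiding".

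Section 2.2.4 explains why first-void urine was chosen. Mucus and exfoliated-cell debris from the genital tract collect around the urethral opening and "are washed away mainly with the urine initial flow (first-void urine"). The questionnaire in Section 11.1 asks for "Time since last urination (before taking the FV sample").

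Urine is one of the five specimen types in the primary objective. Section 9.1.1.2 pools the two cohorts for it: "Oral, vulvar, urine and anal samples included in the HPV-RIFT1 and HPV-RIFT2 cohorts will be analyzed together to obtain the minimal sample size" set for that analysis.

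**The concern.** The instruction on order and the instruction on collection pull against each other. A woman who passes urine for the pregnancy test on arrival, and is then asked for the study urine at the same visit, has voided within the interval that Section 8.2.1.3 is meant to keep clear. The initial flow, which is the reason for choosing first-void urine, has by then gone into the test container.

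What is at stake is the urine part of the primary objective. Section 9.1.1.1.2 admits a case only if HPV16/18 DNA and virions are detected before and after vaccination and, after vaccination, if exuded antibody is also detected. Material lost to an earlier void could turn a sample negative on any of these and remove it. The protocol already pools cohorts to reach a minimal sample size for urine, so there is little room for avoidable loss.

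**Working it through.** The point is about order and rests on no power or alpha calculation, and the protocol states no figure to reproduce. The check is to list the ways in which a site could carry out a visit and compare each with the text.

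| Conduct of the visit | Section 8.2.1.3 (at least 2 h) | Section 4.1 (test before any sample) | Initial flow | Provided for in the protocol? |
|---|---|---|---|---|
| (a) Two voids less than 2 h apart, test first | Broken | Met | Used for the pregnancy test | It is what results from the written order with nothing added |
| (b) Two voids at least 2 h apart, test first | Met | Met | The second void has its own initial flow after the required interval | No wait is scheduled |
| (c) One void after at least 2 h, initial fraction kept for the study, remainder tested | Met | Departs from the literal order, because the study urine is collected before the test is done | Kept for the study | No split void is mentioned |

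Only (b) satisfies both sections literally, and it needs a wait that no section schedules. Option (c) is practicable but goes against Section 4.1 as worded. A site that follows Section 4.1 and adds nothing arrives at (a). The protocol does not say which of the three applies.

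Does another rule catch (a)? Section 8.5.3 sets conditions for sample visits (no sexual activity in the previous 48 h, no menstruation) and requires rescheduling if they are not met. The voiding interval is not among them. The questionnaire records the interval but attaches no consequence to a short one.

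Reach, at the minimum enrolment and assuming every woman attends every visit:

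- Women: 39 + 30 = 69.
- Scheduled urine samples under the conflicting order: 69 × 4 = 276.
- Urine samples in the primary comparison of Visit 1 with Visit 4: 69 × 2 = 138, before the exclusions in Section 9.1.1.1.2.

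These figures count samples to which the order applies, not samples lost. The loss would need the share of sites or visits that follow (a) and the drop in detectable material after a recent void. The protocol gives neither.

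Effect on the stated sample sizes: Section 9.2.1 sizes the first cohort on cervical samples and Section 9.2.2 sizes the second on anal samples. Neither uses urine, so neither figure changes.

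**The case against.** The strongest reply is that the text orders the pregnancy test, not a separate void. The Schedule of Activities lists activities by visit, without clock times or a count of specimens, and the list in Section 4.1 is a summary. The specific rule is in Section 8.2.1.3, and a site that respects it has to wait or split one void. The questionnaire item shows that the designers had the interval in mind. It is completed at Visits 1 and 4 even under the narrower statement in Section 4.1 (the Schedule ticks all four), so short intervals would be visible at both visits of the primary comparison. Section 9.1.3 also leaves room for sensitivity analyses using questionnaire data.

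Much of this stands. It rules out three stronger readings that a reader might reach:

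- *That the study urine is in fact a second void and has lost its washings.* No section says that two voids are made or that they fall within 2 h of each other. This is what the written order leads to if nothing is added, not something the protocol states.
- *That a second void keeps only a minority of the material.* Section 2.2.4 contrasts the initial flow with the rest of one stream. It does not compare a first void with a later one, which has an initial flow of its own.
- *That the before-after change in urine is biased.* The written order is the same at all four visits and the comparison is within each woman. A constant order costs yield and adds noise. Bias would need voiding intervals that differ between visits, and nothing in the protocol shows that they do.

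The objection does not remove the conflict itself. Section 4.1 puts the test before any sample is collected, study urine is one of those samples, and neither way of reconciling this with the 2 h rule is written down. Recording the interval allows a problem to be found afterwards but does not prevent it, and the protocol states no rule for handling a short interval.

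**Conclusion.** The point holds in conditional form. Unless a site adds a 2 h wait or splits one void, following the written order makes the study urine a second void inside the 2 h interval, with the initial flow already used for the pregnancy test. This is more than a missing detail, because a stated order works against a stated collection rule for one of the five primary specimen types.

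The likely consequence is a lower yield of urine samples that meet the analysis criteria, and added noise. Its size cannot be derived from the protocol. The conclusion concerns urine only; the cervical, anal, vulvar and oral analyses and both stated sample sizes are unaffected. It rests on reading the order in Section 4.1 literally and on the absence of any wait or split-void instruction in the protocol. A site manual, if one exists, might already settle it, but the protocol would still need to agree with it.

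**What to change.** Reconcile Sections 1.2.2, 4.1, 8.2.1.3 and 8.3.2 so that they state the following:

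1. One void per visit, after at least 2 h without voiding, serves both purposes.
2. The initial fraction, collected with the Coli-Pee device, is set aside for the study, and the remainder is used for the pregnancy test.
3. The test result is known before vaccination and before the other samples are collected. Section 4.1 should name the initial urine fraction as the one exception to its order.
4. The same order applies at all four visits.

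The cost is a wording amendment and a short site instruction. It adds no visit and no extra specimen, and the pregnancy result stays ahead of vaccination. It assumes that the remainder of the void is enough for the test; the protocol gives no volumes, so the site should confirm this.
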